## Discussion

3

This article outlines the protocol for the Parkinson’s disease risk survey in Thailand which will implement screening of the national population for early signs of PD using a digital platform. Results of validation tests have demonstrated both the validity and reliability of the digital platform that comprises a symptom questionnaire and objective tests of a range of motor tasks, for population screening in both community and hospital settings, and its ability to discriminate between people with and without signs of PD. The first field study was undertaken in Nakhon Sawan Province in January 2024 and the survey is being rolled out throughout Thailand to all citizens over the age of 40 years. Data collection from individual citizens, from further provincial field tests, and from hospital screening stations is ongoing. Data collected from the survey will be used to identify subjects who have either prodromal PD or early signs of clinical PD.

Identification of strategies that could slow the human aging process, and thereby reduce the occurrence and impact of the many chronic noncommunicable diseases, such as PD, associated with advanced age, would undoubtedly have huge societal benefits, and have therefore been the focus of considerable research.

Lifestyle interventions that have been evaluated for their positive benefits in both health and disease prevention include exercise, dietary modifications and sleep. Looking at the available evidence for the benefits of these interventions, in healthy subjects, an 8-week treatment program that included diet, exercise and sleep guidance was shown to have a positive impact on parameters of aging (148). Analysis of patterns of DNA methylation, a recognized biochemical marker of age, in participants was used to calculate their DNAmAge. The program of lifestyle interventions was associated with a statistically significant 3.23-year decrease in subjects’ DNAmAge compared with controls, a potential reversal of epigenetic age.

In the neurology field, various lifestyle interventions have been assessed for their ability to prevent or slow the progression of dementia, and to reduce the risk of developing Alzheimer’s disease and other conditions, including PD, that have protein accumulation pathology (149, 150). A systematic literature review that evaluated studies of multidomain lifestyle interventions (diet, physical activity and cognitive training) on cognitive outcomes in older adults, including those at risk of dementia found that these strategies had beneficial effects in preventing or delaying cognitive decline (151). In the case of PD, it is suggested that for patients identified in the prodromal or very early stage of PD, relatively simple lifestyle modifications that focus on consuming a healthy diet (EAT), increasing engagement with exercise (MOVE), and getting sufficient good quality sleep (SLEEP), might have a more beneficial and timely effect in terms of overall outcomes than waiting to treat established disease (12). Although such interventions rely heavily on patient adherence, they are also relatively risk-free and easy to implement.

Those subjects identified in this first phase of the national screening program as having prodromal PD, will subsequently be targeted in the second phase with EAT, MOVE, SLEEP lifestyle interventions on an individual case-by-case basis under the direction of a neurologist alongside monitoring of intermediate and longer-term outcomes. To achieve this on a national scale, we plan to utilize the existing Thai Red Cross Society network, which is available in all provinces in Thailand to facilitate implementation and monitoring of interventions. This approach was successfully applied by the ChulaPD team for the deployment of a laser cane for PD patients with freezing of gait. Using this collaborative network, it was possible to distribute laser canes to patients all over Thailand, achieving benefits in terms of Social Return on Investment of 2.17 (105, 152). However, it is recognized that implementing any such interventions in real-life, population-based settings is associated with many challenges, not least subject adherence to the proposed program, and each intervention type has its pros and cons depending on individual circumstances (153). In addition, it is likely that the implementation process for lifestyle interventions will need to be adapted to local needs and the situation in individual provinces.

Evidence of the benefits of each of the aforementioned lifestyle interventions in neurological diseases is summarized below.

### Eat

3.1

Various different dietary styles and the use of nutritional supplements have been investigated for their potential to slow the development and progression of PD, and as part of the management of established disease, although data are primarily from observational studies (154–156). There has been increasing interest in “food as medicine” and how dietary components, in particular plant-derived compounds, might attenuate dopaminergic neuron degeneration, reduce α-synuclein aggregation, and modulate neuroinflammatory responses in people with PD (157, 158). A study undertaken in Greece assessed the probability of prodromal PD in a population-based cohort of older adults using MDS research criteria and investigated its possible association with consumption of a Mediterranean diet (159). This dietary style focuses on consumption of high fiber vegetables, fruits, herbs, nuts, beans and whole grains, with moderate amounts of dairy, poultry, eggs and seafood, but a low intake of red meat. A significantly lower probability for prodromal PD was observed in subjects who had high scores for adherence to a Mediterranean diet, and this was related primarily to nonmotor markers, such as depression, constipation, urinary dysfunction, and daytime somnolence. Notably, subjects in the highest adherence quartile had a 21% lower probability of prodromal PD than those in the lowest adherence quartile. Analysis of data for over 47,000 participants in the Nurses’ Health Study and the Health Professionals Follow-up Study in the USA found that adherence to a Mediterranean-style diet was associated with a delay in the onset of is some prodromal nonmotor PD symptoms (160). A large study from China including over 71,000 participants examined the association between overall diet quality and prodromal PD features (161). Diet quality was assessed using the modified Alternative Healthy Eating Index and alternate Mediterranean diet (aMED). Better diet quality was associated with lower probability of having prodromal PD features, including daytime sleepiness and constipation. A prospective observational study, Complementary and Alternative Medicine (CAM) Care in PD, included over 1,000 subjects and found that the foods associated with the reduced rate of PD progression included fresh vegetables, fresh fruit, nuts and seeds, non-fried fish, and olive oil (162), which align with the components of a Mediterranean-style diet. A recent systematic review has suggested that dietary flavonoids, which are known to be abundant in fruits and plant-based foods, may prevent or slow PD progression due to their antioxidant properties (163). In the case of Thailand, a “Thai-Medi diet” has been proposed for people with PD to capture the recognized benefits of the Mediterranean diet but adapted to include local ingredients that maintain the unique taste of Thai food that will be acceptable to Thai citizens (158).

The importance of bidirectional communication between the gut and the brain, the so called gut–brain axis, and the composition of the gut microbiome, is the subject of considerable ongoing research interest in terms of the relationship to the pathological mechanisms that underlie PD (164, 165). It is hypothesized that PD may in fact original in the gut which aligns with observations that various types of gastrointestinal dysfunction (e.g., dysphagia and constipation) are prodromal features of PD. The composition of the intestinal microbiota in people with PD is characterized by a loss of short chain fatty acid bacteria and increased lipopolysaccharide bacteria. Diet inevitably has a huge influence on the composition of the gut microbiome and data suggest that components of a Mediterranean diet, including high levels of fiber, bioflavonoids and omega-3 fatty acids, have beneficial effects on the gut microbiome composition and intestinal cell function, which in turn has positive effects on the brain, including anti-inflammatory and antioxidant effects (164, 166). Similarly, restoration of the gut microbiome using probiotics, prebiotics or other dietary supplements has also been suggested to have the potential to slow PD progression (167).

### Move

3.2

The best studied lifestyle intervention in terms of its potential positive impact on the development of PD, and treatment of early disease, is physical exercise, particularly vigorous aerobic exercise (153, 168, 169). The mechanisms underlying the effect of exercise on PD remain to be fully elucidated, but it is known to be associated with a higher quality of life in PD patients and is thought to result in protective and stimulatory effects that lead to better functional efficiency in higher-level cognitive networks (170). Improvements in muscle strength from regular exercise also improve balance and motor function. Physical exercise is also known to be an effective strategy to strengthen motor reserve and for developing “neuronal resilience” so that individuals are better able to cope with neurodegeneration as they age (171).

One of the histopathological characteristics of PD is the presence of Lewy bodies in brain tissue comprising aggregates of α-synuclein that are thought to contribute to the progressive loss of dopaminergic neurons (172). At a cellular level, studies have shown that exercise can induce autophagy, the process that results in lysosomal degradation of unwanted products. Studies in people with PD have shown that exercise-induced autophagy can decrease the accumulation of toxic α-synuclein aggregates, thereby delaying the progression of motor symptoms of the disease (173). Other suggested mechanisms for the effects of exercise on PD pathology include the reduction of inflammation and oxidative stress and enhancement of nerve regeneration and mitochondrial function (174).

In the clinical setting, accumulated evidence suggests that moderate-to-vigorous exercise may have a protective effect against the development of PD (175, 176). A study has also shown that the amount of exercise engagement prior to a diagnosis of PD can in fact enhance motor reserve once the disease is established, meaning that patients will have less motor deficits for similar degrees of dopamine depletion (177). Several studies have evaluated the effect of exercise in slowing the progression of early PD. SPARX (Study in Parkinson Disease of Exercise) was Phase 2, multicenter randomized clinical trial of patients with *de novo* PD who were not yet taking any medication to determine the impact of high-intensity treadmill exercise for 4 days per week (178). This exercise regimen resulted in better Unified Parkinson’s Disease Rating Scale (UPDRS) motor scores compared to patients who underwent moderate or no exercise. SPARX3, a multicenter, randomized Phase 3 clinical trial, is now ongoing to determine the ability of high-intensity endurance treadmill exercise to slow the progression of PD as assessed by evaluation of the MDS-UPDRS motor scores (179). The effects of long-term exercise intervention are currently being evaluated in the CYCLE II (Cyclical Lower Extremity Exercise for Parkinson Disease II) study a 2-site, randomized controlled trial (180). Patients will be randomized to in-home aerobic exercise sessions using an exercise bike three times per week for 12 months or usual care, and the change in the MDS-UPDRS motor score over that time will be assessed and compared in the two groups. The current consensus, therefore, is that exercise should form an essential part of the initial therapeutic strategy for early PD—the concept of “exercise as medicine”—in particular aerobic exercise and resistance training (181), but that it may also have a role in both primary and secondary disease prevention (182).

### Sleep

3.3

According to a position statement issued by the American Academy of Sleep Medicine (AASM), sleep, of good quality and an adequate quantity, is something that is essential to people’s health and wellbeing (183). Similarly, lack of sleep, or experiencing sleep disorders that disrupt the body’s normal circadian rhythm, can have a significant negative impact on both physical and mental health (184). At a cellular level, adequate sleep is important to enable the restoration, regulation and repair of key neural process and to ensure good cognitive function, and there is now accumulating evidence that poor sleep may be associated with the development and progression of some chronic diseases, such as cardiovascular disease and Alzheimer’s disease (184), so it is probable that the same could be true for PD. Similarly, disruption of sleep and circadian rhythms are known as key factors in neurodegeneration, and their occurrence during early PD stages suggests a causal role in the disease pathogenesis (185). Notably, preclinical data suggest that a contributor to the restorative effects of sleep may be its removal of potentially neurotoxic waste products that accumulate in the central nervous system while awake (186). Recognizing the important bidirectional relationship between sleep, health and disease, the AASM recommends that healthy sleep should be a key target for education and public health initiatives. Similarly, the American Heart Association includes sleep duration as a vital component of its “Life’s Essential 8” as a metric for cardiovascular health (187). A recent review of studies in people with mild cognitive impairment or Alzheimer’s disease found that sleep problems such as obstructive sleep apnea as well as sleep duration had strong pathophysiological links with the development of dementia (188). A number of small studies have also suggested a positive relationship between sleep and physical exercise, in that exercise may reduce the negative consequences of poor sleep on cognitive function, and conversely that sleep may be a mechanism by which exercise can improve cognitive function (189). Sleep problems are common nonmotor PD symptoms and can be observed in both the prodromal and early stages (190). The most common sleep disorders are insomnia, sleep disordered breathing, excessive daytime sleepiness, RBD, and sleep-related movement disorders, such as restless legs syndrome (191). We know that RBD is a strong predictor of subsequent PD (60, 62), therefore early detection of sleep problems in older people, in particular RBD, may provide an opportunity for early intervention to treat the sleep disorder itself and to prevent the development of PD. While evidence for direct preventative effects of sleep on PD are limited, it is a logical proposition that improved sleep quality will improve overall symptoms of the affected individual and potentially delay the development/progression of PD.

People who are identified by the Parkinson’s disease risk survey model as having early signs of PD will be referred to a neurologist for clinical examination and confirmation of PD through the network of National Health Security Offices and the Thai Red Cross Society. If a diagnosis of PD is confirmed, they will be referred for treatment according to their healthcare plan (12).

The model developed for the Parkinson’s disease risk survey combines multimodal features with machine learning analysis of both questionnaire responses and results from objective measurement of symptoms to provide a composite score for the risk of PD. This multimodal approach has been used previously with high accuracy for the preclinical diagnosis of PD. While the heterogeneity of datasets obtained from multiple sources challenges the classical approach to data analysis and interpretation, it also provides new opportunities for extracting valuable information using machine learning tools. The Parkinson’s Progression Markers Initiative (PPMI) database is a good example of this, being a large archive of Big Data, both structured and unstructured (192), and the significant information that can be generated using this approach. Using machine learning tools, PPMI data for 401 subjects with early PD dopaminergic imaging markers were used to classify early PD (193). The SVM classifier used in this study resulted in an accuracy of 96.40% with 97.03% sensitivity, 95.01% specificity, and 98.88% area under ROC curve. Another study, also using data from the PPMI database, constructed a diagnostic using eight different variables, namely age, gender, family history, University of Pennsylvania Smell Inventory Test score, Montreal Cognitive Assessment score, RBD Screening Questionnaire score, levels of α-synuclein in CSF, and SNCA rs356181 polymorphism (194). The model had a high accuracy for identifying early PD with an AUC of 0.93. Several reports now suggest that digital models that integrate multidimensional data, as has been done with the Parkinson’s disease risk survey model, may in fact significantly enhance the performance of PD prediction (195, 196).

Our study uses population screening with digital technology which is associated with certain challenges and limitations. With the rapid rise in the use of digital technologies in healthcare, digital health literacy, namely the ability of an individual to interact with health information on the internet or in other digital formats, is becoming increasingly important. However, digital health literacy and competence in using these tools among older people, especially in LMICs such as Thailand, is often low (197, 198), which might impact uptake of the survey. In contrast, the use of smartphones and other digital technologies among elderly people is on the rise and reported to have positive effects on their self-rated health (199), In the case of Thailand, a survey of smartphone use undertaken in 2022 found that around 77.3% of respondents aged 50 years and over used a smartphone (200), which would suggest that adoption of digital screening in Thailand is very feasible. It is also recognized that continued training of the machine learning models used for data analysis in our study will be necessary to improve the accuracy of PD diagnosis and, importantly, to avoid overdiagnosis. Further studies will be needed to determine if the model can differentiate between PD and atypical parkinsonian disorders. Currently, the model in its present iteration cannot differentiate between PD and prodromal patients, so is unclear whether prodromal patients will be classified as PD patients or as normal subjects.

While the Parkinson’s disease risk survey is an Asian initiative, data acquired from this national study will contribute to the evidence base for disease preventive strategies globally. Sharing this information and experience is an essential part of the global collaborative effort needed to meet the challenge of PD. This approach could also serve as a model for disease prevention efforts for other types of non-communicable diseases in LMICs. The healthcare system in Thailand has been ranked highly by various international agencies including the Global Health Security Index (12, 201–203) and is therefore suitably placed to take on the challenge of disease prevention in line with the WHO’s strategic objectives for overall population health, and PD in particular (17, 41, 42).

In conclusion, the Parkinson’s disease risk survey digital platform offers a robust, validated method with high accuracy for national screening of the Thai population for signs of PD. This provides a window for timely intervention to minimize the number of cases that progress to clinical PD and effective early treatment of those confirmed with early PD. Large scale implementation is possible with a strong linkage between multiple stakeholders who are involved with the care of PD. These objectives align with calls from global organizations, such as the WHO, for a greater focus on preventative strategies for PD in efforts to stem the steep rise in prevalence. If implemented successfully, the Parkinson’s disease risk survey could act as a model for screening strategies for other non-communicable diseases in Thailand, and elsewhere.

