### The Thai Parkinson’s disease risk survey

1.7

The Parkinson’s disease risk survey (Thai Clinical Trials Registry identification number: TCTR20231025005) is being undertaken to evaluate a digital population screening platform that will allow identification of undiagnosed cases of PD, which may include early and more advanced cases, within the Thai population aged over 40 years. It is also hoped that the study will identify those in the prodromal stage as well as at-risk individuals who can be targeted with preventive lifestyle interventions. The overall rationale and objectives of the national digital screening program and its expected outcomes are outlined in Figure 2.

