**Figure 3 fig3:**
[figure not shown]
The Parkinson’s disease risk survey project implemented in honor of [name], Executive Vice President of Thai Red Cross Society. Top: Her Royal Highness and the multidisciplinary team involved in the study’s design, validation, and implementation at the official opening event; bottom: subjects being screened with the digital tools.

Prodromal PD refers to the stage at which individuals do not fulfill diagnostic criteria for PD (i.e., bradykinesia and at least one other motor sign) but do exhibit signs and symptoms that indicate a higher-than-average risk of developing motor symptoms and a diagnosis of PD in the future (62). The digital platform will be deployed nationally and allow the collection of data on the person’s speech, hand tremor, finger dexterity, and mobility, which will be analyzed alongside information obtained from a questionnaire about PD symptoms completed by the participants. The outcomes will enable a range of lifestyle interventions to be implemented in those determined to be at risk of developing PD in the future or suitable treatment for those considered to have early PD.

Evidence is emerging that interventions such as regular exercise, consuming a more Mediterranean-style diet, and ensuring adequate sleep quality can potentially help slow disease progression and the transition from the prodromal stage to clinical PD. Once subjects who may have prodromal have been identified through national screening (Phase 1 of the project), these lifestyle interventions—namely EAT, MOVE and SLEEP—can be implemented subsequently on a personalized basis with the objective of preventing or minimizing the development of PD within Thailand (Phase 2 of the project) (12). It is anticipated that this digital platform could also act as a model for similar screening strategies for other non-communicable diseases in Thailand.

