Data collected via the digital platform is stored in a database created and managed by the Thai Red Cross Society, strictly in accordance with the relevant Institutional Review Board and Personal Data Protection Act regulations. The Thai Red Cross Society is a major national non-profit public organization that undertakes humanitarian activities, including those related to the promotion of quality of life and disease treatment and eradication, in keeping with the principles of the International Red Cross. The Society is closely affiliated with ChulaPD, the only tertiary center in Thailand dedicated to the study and care of PD, with whom they have collaborated over many years on national projects related to PD and its management (28, 107).

Identification of individuals who may have undiagnosed PD (both early and more advanced), those who may be in the prodromal stage, or those at risk of developing the condition will be evaluated by different machine learning models using combined data from the questionnaire and objective measurements.

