#### Digital marker validation and data analysis

2.3.2

The eight selected markers have been developed into a digital application that has been validated as described below. Validation was undertaken in a cohort of 343 people with PD (48.6% male) and 230 control subjects (27.9% were male) without PD. Participants undertook each test activity using a mobile application and data were recorded using the built-in sensors of the mobile phone, namely the accelerometer, gyroscope, microphone, and touch screen. The validation study was approved by the Human Ethics Committee of the Faculty of Medicine, Chulalongkorn University (IRB number 0804/65). All subjects gave written informed consent before the enrolment into the study, in accordance with the declaration of Helsinki. Performance on the eight test activities were recorded by each participant using a mobile application and the built-in sensors of a smartphone, namely the accelerometer, gyroscope, microphone, and touch screen. Details of how each testing activity was performed is described in Table 5.

**Table 5 tab5:** Performance methods for each of the digital marker test activities.

Marker	Description of test
Voice vowel	Participants pronounce the sustained vowel /a/, as in “*bar*,” for 10 s without holding their breath. The test is repeated three times for each participant.
Voice sentences	Participants read sentences aloud in the Thai language, such as the example sentence “*rod tid mak loey*,” which means “*The traffic is really jammed*.” The test includes a total of 25 sentences that are commonly encountered in real-life situations.
Resting tremor	Participants are instructed to place the mobile phone on one palm with the screen facing up and lay their hand in their lap. They are then asked to specify whether the device is on the left- or right-hand side by pressing on the screen. Finally, participants are instructed to keep their hand still, along with the device, for 20 s.
Postural tremor	Participants are instructed to hold the device and press on the screen to verify which side of the hand they are holding, then stretch out their arm and maintain that posture for 20 s.
Alternate finger tapping	Participants place the device on a flat surface. They are then instructed to use their index and middle fingers of one hand to tap on two circles that appear on the screen, alternating between the two fingers as quickly as possible while maintaining correct finger alternation within 10 s.

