##### Choice of machine learning classifier

2.3.2.2

Many studies have demonstrated the effectiveness of using machine learning classification algorithms to accurately differentiate individuals with and without PD based on data collected through smartphone applications.

Initially, the performance of three machine learning classifiers was compared: multilayer perceptron (MLP), SVC, and random forest (RF) using the hold-out method for dataset splitting, to find which would be best suited for the Parkinson’s disease risk survey data. We used the default settings for each classifier from scikit-learn (143) version 1.3.0. The RF algorithm was chosen because it demonstrated higher accuracy in classifying PD compared to SVC and performed comparably to MLP in our preliminary analysis using tremor and gait recordings. The superior performance of the RF algorithm compared to SVC and MLP aligns with the findings of Sarkar et al. (144).

RF is a machine learning algorithm composed of an ensemble of decision trees. In a classification task, each branch of the decision tree is trained using subsets of sampled training data labeled by the predicting classes. During the learning process, decision trees perform a series of comparisons on selected input features (node splitting) until a predicting class is assigned to the feature. The final predicted class of the RF is determined by the majority of the output classes from the decision trees.

In the validation study, an RF classifier was used to predict whether activity recordings were from a person with or without PD. The forest consisted of 100 trees, and Gini impurity was used to measure the quality of splits. The maximum number of features was determined by the square root of the total number of features before searching for the best node splitting. Ten-fold cross-validation was employed to assess the generalizability of the classifiers. In each test activity, the data was divided into 90% for training and 10% for testing sets. Classifiers trained specifically for a type of activity are referred to as specialized classifiers.

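### Phase 1 is said to identify prodromal people for Phase 2, but the only classifier described outputs PD or non-PD, and the article concedes it cannot separate PD from prodromal

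*Protocol article*

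**What the plan says.** **What is promised.** Section 1.7 puts undiagnosed PD first and adds the rest as an aspiration: "It is also hoped that the study will identify those in the prodromal stage as well as at-risk individuals". Later text is firmer. Section 2.1 says that, besides people with undiagnosed PD, "those who may be in the prodromal stage, or those at risk of developing the condition will be evaluated by different machine learning models". The Discussion opens with "Data collected from the survey will be used to identify subjects who have either prodromal PD or early signs of clinical PD", and a few paragraphs on makes that label the route into the lifestyle interventions: "Those subjects identified in this first phase of the national screening program as having prodromal PD, will subsequently be targeted in the second phase".

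**What was built.** Section 2.3.2 gives the data: "Validation was undertaken in a cohort of 343 people with PD (48.6% male) and 230 control subjects (27.9% were male) without PD". Section 2.3.2.2 gives the target: "an RF classifier was used to predict whether activity recordings were from a person with or without PD". Section 2.3.2.3 combines the activity-specific models by majority vote into one of the same two classes, and section 2.3.2.4 defines every metric on those two classes.

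**What is conceded.** The limitations paragraph, printed after section 3.3, says that "the model in its present iteration cannot differentiate between PD and prodromal patients". It adds that the side on which prodromal people will land, PD or normal, is not known.

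**The concern.** A stated product of Phase 1 is a set of people labelled prodromal, and section 2.1 adds people at risk. The method described yields two labels, and neither was built to represent those groups. The article defines the prodromal stage so that such people fall outside the PD label: "Prodromal PD refers to the stage at which individuals do not fulfill diagnostic criteria for PD". They are not typical controls either, because the same definition gives them signs that raise their risk.

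Two things are at stake. First, any count of prodromal people reported from the classifier would have no known error rate. Second, Phase 2 entry depends on that label, so the people targeted would be selected by a rule whose behaviour in them has not been measured. Field work has already begun, so the text should be put right before survey results are reported under these labels.

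**Working it through.** No sample-size or power figure is involved. The check sets the stated outputs beside the classifier as described.

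**1. Groups the text says will be identified**

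- Section 2.1: three groups, namely undiagnosed PD (early and more advanced together), prodromal, and at risk.
- Opening of the Discussion: two groups, namely prodromal PD and early clinical PD.
- Phase 2 entry (Discussion): the prodromal group.

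**2. Groups in the validation data (section 2.3.2)**

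- PD: 343. Controls without PD: 230. Total: 343 + 230 = 573.
- Prodromal or at-risk: none reported as a group.

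**3. Output of the model**

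- Each activity-specific random forest: with or without PD (2.3.2.2).
- Ensemble vote: PD or non-PD (2.3.2.3).
- AUC, true positive rate, true negative rate and accuracy: PD positive, non-PD negative (2.3.2.4).

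So there are two output labels against three groups in section 2.1.

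**4. What the reported performance covers**

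Table 6 gives AUCs from 0.82 (voice vowel) to 0.88 (balance). Table 7 gives a best ensemble accuracy of 0.9108. Both describe PD against non-PD, and neither contains information on how a prodromal person is voted.

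**5. What follows for a prodromal group**

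Let *s* be the probability that a prodromal person is voted PD. Suppose the screened population contains *M* prodromal people and *H* people with neither PD nor prodromal PD.

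- Prodromal people voted PD: *M* × *s*.
- Prodromal people voted normal: *M* × (1 − *s*).
- People with neither condition voted PD: *H* × (1 − TNR), where TNR is the true negative rate in that group.

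Suppose neurologist examination removes all confirmed PD from the screen-positives. The prodromal share of the remainder is then

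*M s* / [*M s* + *H* (1 − TNR)].

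The limitations paragraph leaves *s* open, so on the document's own terms it may lie anywhere from 0 to 1. At *s* = 0 the remainder contains no prodromal people and all of them are missed. At *s* = 1 none is missed, but they remain mixed with false positives in an unknown ratio, because *M*/*H* is not given either. The composition is therefore not identified.

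**6. Whether another step recovers them**

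The referral paragraph after section 3.3 sends people whom the model finds to have early signs of PD to a neurologist, to confirm PD. It describes no such step for people voted normal, so the *M* × (1 − *s*) group has no described route to being found.

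**The case against.** **The limitation is disclosed and tied to the present version.** That is true, and section 1.7 only hopes to find prodromal cases. But section 2.1 and both Discussion statements say this will be done, and Phase 2 depends on it. Disclosure does not reconcile those passages. The further training foreseen is aimed at accuracy of PD diagnosis and avoiding overdiagnosis, not at adding a prodromal class.

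**Other models or a score may exist.** Section 2.1 speaks of several models, and the Discussion of a combined risk score. This stands in part: the binary forest is the only classifier described, not provably the only one. But no prodromal class, cut-off, reference standard or validation is given for any alternative.

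**A neurologist is involved.** This stands for screen-positives: a flagged person without confirmed PD may be truly prodromal, and Phase 2 is under neurologist direction. It does not reach people voted normal.

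**An article condenses, and Phase 2 selection may have its own protocol.** Missing scoring detail would be no finding. The point here is that the article states an output and also states that its model cannot make the distinction.

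**Stronger readings that a reader might infer, and that the document does not support:**

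- *The model cannot detect prodromal people at all.* The stated inability is between PD and prodromal. Separation from normal is called unclear, and at-risk people are not mentioned there.
- *Anyone labelled prodromal would be a false-positive control or a missed PD case.* Truly prodromal people may be among them, in unknown proportion.
- *None of the 573 was prodromal.* None is reported, but controls are described only as without PD, so unrecognised prodromal cases are possible.
- *The likelihood ratios in section 2.2.2 already give a usable score.* Their product is 6.4 × 2.8 × 2.7 × 2.5 × 1.6 = 193.5, but multiplying them assumes independence. The article gives no ratios for negative answers, no priors and no threshold.

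**Conclusion.** The concern holds as an internal contradiction. Section 2.1 and the Discussion attribute to machine-learning evaluation of the survey data an identification of prodromal people, and in section 2.1 of at-risk people. The classifier described does not return those labels, and the article says it cannot separate prodromal from PD.

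Its size is this: two output labels against three stated groups, no prodromal group reported among 573 validation participants, and prodromal sensitivity and specificity not estimable. A prodromal group derived from the vote would be of unknown composition and would omit any prodromal people voted normal. No reported performance figure is affected, because all of those in section 2.3.2.5 concern PD against non-PD.

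The conclusion assumes that the classifier in sections 2.3.2.2 to 2.3.2.4 is the one applied to the survey, since no other is described. A further model with its own prodromal validation would change it. So would a full protocol that defines prodromal status by another route.

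**What to change.** 1. Reconcile section 2.1 and the two Discussion statements with the limitations paragraph. State the classifier's output, and the Phase 1 conclusion that rests on it, as screen-positive or screen-negative for PD. The closing paragraph already speaks of signs of PD, but its next sentence, on reducing progression to clinical PD, needs the same limit.
2. Remove prodromal and at-risk status as classifier outputs unless and until a model is validated for them against a stated reference standard.
3. Do not let any prodromal label used for Phase 2 rest on the PD/non-PD vote. One option is a separate, prespecified prodromal probability based on the research criteria the article already cites, using questionnaire items 11 to 15. Two caveats should be written beside it: the article does not show that the likelihood ratios are independent, nor that they apply to these single yes/no items. Priors, ratios for negative answers and a threshold would also have to be specified. Undetected PD among people who are not examined would remain in such a group, and this should be said.

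Items 1 and 2 cost protocol wording only. Item 3 uses questionnaire answers already collected, but the scoring takes real specification work. The downside is a narrower claim for the machine-learning model.
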